## Abstract

**Clinical Trial Registration:**

[www.ClinicalTrials.gov], identifier [NCT05126823].

## Introduction

Cancer continues to be a relevant health problem worldwide. Despite advances in diagnostic, prevention and treatment techniques in recent years, cancer continues to appear as one of the leading causes of mortality worldwide, only behind cardiovascular disease (World Health Organization, 2021). Specifically, cancer caused 9.96 million deaths in 2020, with lung (18%) and colorectal cancer (9.4%) having the highest mortality rates. This pattern was also observed in Spain, where 113.054 people died of cancer, with lung and colorectal cancer having the highest mortality rate. Regarding the incidence, estimates predict that in the coming years a very significant increase in cases (+49.2%) will be observed worldwide, going from an estimated incidence of 18.094.716 in 2020 to 26.997.577 in 2040. In Spain, the data show a relatively stable trend with ascending values, since in 2021, for example, 276.239 cases were diagnosed and by 2022 it is estimated that 280.100 new cases will be diagnosed, but this data are probably influenced by the negative impact of the COVID-19 pandemic during this period. Despite this, the higher incidence rates correspond to colorectal (43.370), breast (34.750), and lung cancer (30.948) (Sociedad Española de Oncología Médica, 2022).

In cancer patients, it is common to observe certain impairments as a consequence of the disease and its treatments. The most frequent psychological symptoms are anxiety (10–18%) and depression (11–20%), which, in addition, are consistently related to a worse quality of life in this group of patients (Satin et al., 2009; Kuhnt et al., 2016; Pitman et al., 2018; De Mol et al., 2020; Erim et al., 2020; Park et al., 2020; Taarnhøj et al., 2020). Fatigue, understood as a subjective state of emotional and physical fatigue that interferes with the patient’s normal functioning, appears in up to 60% of cancer patients, while sleep disturbances, both in the form of insomnia, as in terms of difficulties when falling asleep, and maintaining sleep, is also observed in a high number of patients, in a range between 18 and 68% (Mock et al., 2000; Corbett et al., 2016; Zhou et al., 2017; Yun et al., 2021).

The acceptance and commitment therapy (ACT, Hayes et al., 2011) has shown to be an effective treatment for reducing these psychological symptoms and, thus, beneficial for improving psychological wellbeing in cancer patients. A central principle of ACT is to consider that, while suffering is unavoidable, it can be coped with by using psychological flexibility, defined as “contacting with the present moment as a conscious human being, fully and without needless defense-as it is and not as what it says it is-and persisting with or changing a behavior in the service of chosen values” (Hayes et al., 2011, p. 96–97). Specifically, the intervention with ACT focuses on three mechanisms that contribute, through psychological flexibility, to a healthy adjustment during the course of the disease in cancer patients: (1) being present in the here and now, (2) being opened to contact with emotions and (3) do what matters according to personal values (Fashler et al., 2018). In contrast to other psychological treatments, such as the cognitive behavioral therapy, ACT focuses on changing the patient’s relationship with their negative thoughts, without trying to change these thoughts. In fact, it is common for cancer patients that negative thoughts about the disease, the treatment or the prognosis might be realistic and coherent with their current state and not the product of distorted information processing. In this way, encouraging patients to change the relationship they have with their thoughts rather than trying to modify them can have a positive effect on patients’ adjustment to the disease (Hulbert-Williams et al., 2015; Fashler et al., 2018).

In a recent systematic review of randomized and controlled trials on the efficacy of the use of ACT in cancer patients, applied individually or in groups, the authors observed that this therapy has shown to be effective for reducing symptoms of anxiety, depression, sleep problems, and pain, among others (Bas and Dirik, 2019). A similar review concluded that applying ACT was beneficial for increasing the psychological flexibility of cancer patients, in addition to obtaining improvements in their quality of life and emotional state (González-Fernández and Fernández-Rodríguez, 2019). In this sense, psychological flexibility appears as a key element to explain the therapeutic change after the application of ACT in cancer patients. The results obtained by Aguirre-Camacho and Moreno-Jiménez (2017) suggest that psychological flexibility is the mediating variable of the positive effects of face-to-face interventions in ACT on anxiety, depression and quality of life in cancer patients. These results are supported by different studies in samples with various types of cancer (Feros et al., 2013; Arch and Mitchell, 2016), which highlights the need to consider the psychological flexibility as a therapeutic target in this group of patients, with the aim of improving their emotional adjustment and quality of life. However, despite these promising results, these authors have emphasized that more empirical support from controlled trials with adequate follow-up is needed to establish the efficacy of ACT in cancer patients.

Although the use of non-face-to-face ACT-based interventions might be useful for patients with difficulties in accessing health centers, there is still little evidence of the benefits of this therapeutic modality for cancer patients. The previous literature in this regard shows the positive result of the randomized clinical trial carried out by Hawkes et al. (2014), in which the authors used the telephone as a means to carry out an intervention based on symptom management, coping with stress and training in a healthy lifestyle, compared to a control group that received the usual treatment. The results showed that patients assigned to the ACT group had improvements in emotional wellbeing compared to the group that received no treatment. In a similar intervention, using the telephone as a means to carry out an ACT-based intervention, Mosher et al. (2018) observed that after finishing it, improvements were obtained in the level of depression and anxiety, in addition to lower levels of fatigue and sleep problems in patients with metastatic breast cancer. Therefore, there is evidence that supports the use of non-face-to-face ACT-based interventions in cancer patients, since this format improves results when the interaction with the therapist is allowed (Baumeister et al., 2014).

Relatedly, Arch et al. (2020) carried out a randomized pilot trial with 35 stage IV patients with cancer, applying a combined ACT intervention (4 face-to-face sessions + online sessions), observing that after the intervention the levels of anxiety and depression were significantly reduced. In this line, Feros et al. (2013), using a combined ACT intervention (face-to-face + Compact Disk), in a research design with 28 patients with cancer and without a control group, observed that after the intervention, the patients obtained significant improvements in anxiety, depression, quality of life and psychological flexibility. Despite these positive results, the aforementioned authors highlighted the need to carry out studies with greater control (randomized and controlled trials), a larger sample size and with adequate follow-up to be able to establish the efficacy of the ACT in this group of patients.

In recent years there has been an increase in the use of mhealth applications (apps) in the context of cancer. The massive use of smartphones and the internet favors that users of health systems have direct access to information on aspects related to cancer (prevention, detection, treatment options, etc.), which results in different benefits for patients cancer, as better self-efficacy and empowerment of patients (Charbonneau et al., 2020). In a recent review on the use of apps in cancer patients, the authors concluded that the use of these apps has beneficial effects on symptom control; however, there is little evidence of the positive effect of the use of apps on other outcomes in studies that include interventions (Osborn et al., 2020).

Considering the previously exposed, this study has the following objectives: First, to test the efficacy of a combined psychological intervention (ACT face-to-face + app), in comparison with an ACT face-to-face intervention and a waitlist group, to increase psychological flexibility and to significantly improve scores for anxiety, depression, quality of life, fatigue, insomnia, and post-traumatic growth from baseline to end of the intervention and in the two follow up periods (3 and 6 months after the intervention). And, secondly, to test the efficacy of the face-to-face ACT-based intervention group compared to the waitlist control group in the mentioned variables, to provide further empirical support for the use of ACT in cancer patients.

Consequently, this study has the following hypotheses:

1.The combined intervention (face-to-face ACT + app) will be more effective in increasing psychological flexibility, quality of life and post-traumatic growth and reducing symptoms of anxiety, depression, fatigue and insomnia than the face-to-face ACT intervention at posttreatment and at the two follow-up periods (3 and 6 months).2.The face-to-face ACT + app group will achieve significant improvements in psychological flexibility, quality of life and post-traumatic growth and significant reductions in anxiety, depression, fatigue, and insomnia compared to the waitlist group after the intervention and at the two follow-up periods (3 and 6 months).3.The face-to-face ACT intervention group will significantly increase psychological flexibility, quality of life and post-traumatic growth, and reduce symptoms of anxiety, depression, fatigue, and insomnia compared to the waitlist group after the intervention and at the two follow-up periods (3 and 6 months).

## Methods and Analysis

### Study Design and Settings

This study is a three-arm randomized superiority clinical trial, with a pre-post-follow-up repeated measures intergroup design with a 1:1:1 allocation ratio. Participants will be randomly assigned to one of the following interventions: (1) face-to-face ACT + app, (2) face-to-face ACT and (3) Waitlist control group. For ethical reasons, the participants in the waitlist control condition will be offered the option to receive the treatment protocol. The evaluation will be carried out in four time points: initial evaluation before randomization (pre-treatment; T0), at the end of the intervention (post-treatment; T1), at 3 months after finishing the treatment (T2) and at 6 months after completing the intervention (T3) (see Figure 1).

**FIGURE 1 F1:**
[figure not shown]
Study protocol flowchart.

This clinical trial will be conducted at the Reina Sofía University Hospital of Córdoba (Spain), and the Faculty of Medicine of the University of Córdoba (Spain). This Hospital is reference in the province for cancer care offering to the patients an integral care, including diagnosis, cancer staging, specific oncological treatment, continuous care, palliative care, and disease follow-up. The research group is responsible for the design of the study, the training of the personnel involved in the collection of the data and the application of the interventions, the provision and preparation of all study documents, the supervision of the study, the treatment and analysis of the data obtained, and the communication and dissemination of the results of the investigation.

### Eligibility Criteria

The inclusion criteria for participants are: Men and women, aged between 18 and 70 years/Cancer diagnosis, stages I–III/Cancer type: Breast/Lung/Colorectal/Eligible for or currently receiving cancer treatment/Ability to be fluent in Spanish/Have a smartphone with daily internet access and basic smartphone skills/app handling skills/Not currently participating in another clinical trial/Not currently receiving other psychological treatment.

The exclusion criteria for participants in the trial are: Men and women aged > 70 years/Diagnosis of cancer, stage IV or other types of cancer/Not eligible for treatment/Inability to handle himself fluently in Spanish/Not having a smartphone with daily internet access and/or lack of basic smartphone skills/app handling skills/Currently participating in another clinical trial/Currently receiving other psychological treatment.

### Interventions

The authors have developed a manualized protocol based on the recommendation to implement ACT therapy (Wilson and Luciano, 2014) and previous research with cancer patients (Feros et al., 2013; Arch and Mitchell, 2016). Interventions will be carried out by psychologists with at least master’s degree in clinical psychology, with previous training in psychological intervention in cancer patients and particularly using ACT in these patients. Furthermore, before the intervention starts, the manualized protocol will be supervised by a trained psychologist that works daily with cancer patients. After completing the revision of the manual, the therapist of the trial will receive specific training about how to intervene with cancer patients using ACT. The therapists who are going to carry out the interventions will be supervised by a coordinator with the aim of solving any doubts that may arise during the established coordination meetings.

#### Face-to-Face Acceptation and Commitment Therapy Group

The main objective of the ACT is to develop psychological flexibility, using acceptance strategies, along with mindfulness techniques and different behavioral techniques (Feros et al., 2013). In cancer patients and survivors, ACT helps to cope with situations of distress or fear, and helps people to clarify their values and to commit to living in a more positive way according to them (Arch and Mitchell, 2016). In the face-to-face ACT group, experiential exercises are carried out. Also, metaphors, discussions and assignments are used to promote awareness and flexibility about the thoughts and emotions associated with cancer. This intervention will be carried out in groups of approximately 10 people. It consists of 8 sessions of 1 hour each, which will be developed weekly, over 8 weeks. The sessions will address the key contents, which are organized into 5 specific modules: Psychoeducation and therapeutic relationship; Mindfulness (awareness of distressing thoughts and feelings); Creative hopelessness (contact with the problem and acceptance); The self as context (defusion and deliteralization); Clarification of personal values and commitment to meaningful activities.

Session 1. *Basic principles of the intervention and establishment of the therapeutic relationship.* In this session, the first contact with the group will be established and the basic principles on which the intervention will be based (Mindfulness, relaxation techniques, and components of acceptance and commitment therapy) will be presented. In addition, it will include a brief psychoeducational component on the consequences of the disease in different areas (family, social, work, economy, emotional, and physical).

Session 2. *Psychoeducation and first contact with mindfulness.* This session deepens the previous knowledge of the group on aspects related to cancer: anxiety, depression, insomnia, fatigue, and the experiential avoidance response as coping. The principles on which mindfulness is based will be presented and a brief exercise will be carried out (Raisin exercise).

Session 3. *Creative hopelessness. First contact with the problem and contact with the private events experienced with great discomfort.* The fundamental objective of this session is to establish contact with experiential avoidance. To do so, the principles of acceptance of the present experience assuming that suffering is normal will be described, along with the necessity of questioning the pattern of interaction with the negative aspects of its existence through the creative despair. In addition, a short mindfulness exercise will be carried out: Mindful Walking.

Session 4. *Understanding the importance of a values-based life*. The objective of this fourth session is to begin to clarify the objectives, goals and values that guide the person’s life in a worthwhile direction. It will try to determine what those avoided (even forgotten) values are, the valuable directions to achieve them, and the gradual establishment of a positive and open attitude toward the progressive exposure to the avoided content in relation to what is important for that person.

Session 5. *Defusion and deliteralization of private events “Self-as-context.”* The main objective of this fifth session is to achieve a deactivation of verbal functions or the distancing of the psychological content: to differentiate the domains or dimensions of the self from its behavior (private events or public behavior); differentiate between what is present verbally and what is made present by language; learn to treat thoughts as thoughts, evaluations as evaluations, and memories as memories. It will also include a brief Mindfulness Practice: The Leaves in the River.

Session 6. *Analyze the problem of control and acceptance as an alternative.* The objective of this sixth session is to analyze the usefulness of the cognitive-emotional control strategy; the person experiences the paradox that their actions to solve the problem are giving the opposite result and that the control strategies put in place have threatened their values, thus promoting psychological flexibility with respect to the avoided content.

Session 7. *Values and barriers.* In the seventh session, the focus will be on clarifying the objectives, goals and values that guide the person’s life in a valuable direction. It will try to determine what those avoided (even forgotten) values are, the valuable directions to achieve them, and the gradual establishment of a positive and open attitude toward the progressive exposure to the avoided content in relation to what is important for that person.

Session 8. *Concluding the therapy*. The objective of this last session will be to review the contents and activities carried out to date and resolve any possible doubts that may arise, providing alternatives to cognitive defusion and experiential avoidance.

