#### Face-to-Face Acceptation and Commitment Therapy Group + App

The multimodal ACT (ACT + app) follows the same principles described above, and addresses the same key content, but combines face-to-face sessions with non-face-to-face activities and resources, using a mobile application in order to facilitate access, patient adherence and follow-up. The participants randomly assigned to this group will receive the same intervention program as the face-to-face group described before, with the same characteristics, along with interspersed non-face-to-face activities, which will serve as support for each of the sessions. The non-contact activities will consist of metaphors used in ACT programs (i.e., Dirty glass metaphor/Man in the hole metaphor/The unwelcome party guest metaphor), mindfulness and breathing exercises using audio files, and registration of values. These activities will be delivered weekly using a mobile phone application developed by the authors for this research.

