#### Waitlist Group

This group will receive the usual care during the essay, but the participants in this group will be offered to receive the face-to-face- ACT group intervention + app once the ACT groups finish the planned intervention and after post-treatment assessment.

Any participant in the intervention groups who meets any of the following criteria will be excluded: Participants’ request to left the study/Participants who stop cancer treatment or change their stage to stage IV/Difficulty to continue with the intervention due to the presence of cancer treatment associated symptoms. Participants who receive other psychological treatment during the trial will be excluded, as stated in exclusion criteria.

During the intervention sessions, the therapist will emphasize the need to attend them on a regular basis and carry out assignments, in addition to highlighting the need to attend the different assessment sessions. For the participants in the ACT face-to-face + app group, the activities to be carried out weekly using the application must be marked by the participants themselves once they are finished, so that the therapist can verify that the activity has indeed been carried out in the established period.

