### Sample Size

To determine the optimal sample size, we considered the effect sizes in psychological flexibility obtained in previous works by other authors. A recent meta-analysis (Chunxiao et al., 2020) examined the effect of ACT (including face-to-face and internet-based modalities) on psychological flexibility compared with treatment as usual or waitlist in cancer patients. The results showed a moderate effect size (Hedges’ *g*) of 0.58 at post-treatment. Taking into account these results, a medium effect size of 0.5 (Cohen’s *d*) has been assumed to detect differences between the interventions and waitlist group. Since no software to determine sample size for linear mixed model analyses was available, we used the *f* index of G*Power. Therefore, an effect size of 0.25 (index f) is assumed, equivalent to Cohen’s *d* = 0.5. Thus, with a statistical power of 0.80, an alpha level of 0.05 and a correlation between repeated measures of 0.5, a total sample of 102 participants is required (34 subjects in each group). In order to control the lack of participants during the intervention and evaluation process, based on a previous study (Arch and Mitchell, 2016) we assume a dropout rate of 10%. Consequently, we require to include 112 participants in our study (38 participants per group).

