### Statistical Methods

Data will be analyzed following the intention to treat (ITT) and per protocol approaches. First, ANOVA or chi-square will be performed to compare the sociodemographic variables and the outcome measures at baseline (T0). Second, to examine the longitudinal changes over time (baseline, post-treatment and follow-ups) and the differences between groups in the variables under study, we will use mixed linear models, since these models are more precise than the repeated measures ANOVA (Gueorguieva and Krystal, 2004). In ITT analysis (all randomized patients are included in the analysis), incomplete or missing data will be considered using the maximum likelihood estimation method. In addition, the effect sizes will be calculated by Cohen’s *d* (bias corrected) (Hedges, 1981) as a measure of the differences between the Standardized Mean Changes (SMC) (T0-T1; T0-T2; T0-T3) of the respective groups (Becker, 1988). We will use the formula *d* = *c* ⋅ ([*M*_*pre*_ –*M*_*post*_]/*SD*_*pre*_) to obtain the SMC, where *c* is the bias correction factor, *M*_*pre*_ and *M*_*post*_ are the means of the pre–test and post–test scores, respectively, and *SD*_*pre*_ is the pre–test standard deviation score (Morris and DeShon, 2002). The SMC will be calculated for each group, providing the *d* index of the general effect size from the differences between them (Face-to-face ACT group vs. Face-to-face ACT group + App; Face-to-face ACT group vs. Waitlist group; Face-to-face ACT group + App vs. Waitlist group). Once the analyses have been performed, summary tables will be displayed for all the planned evaluations: pre-treatment (T0), post-treatment (T1), follow-up at 3 months (T2) and follow-up at 6 months (T3). The results will show frequencies and descriptive statistics (the mean, standard deviation and percentages) to summarize the characteristics of both the total sample and the participants that make up each of the three groups. Finally, the results of the study will be shown in accordance with the 2010 statement of the Consolidated Standards of Reporting Trials (CONSORT) (Moher et al., 2010; Schulz et al., 2010).

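### Both ACT arms are treated in therapy groups of about 10, but the sample size assumes independent patients and the described mixed model names no therapy-group term

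*Protocol article*

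**What the plan says.** All references are to the protocol article. Patients are randomised individually to three arms, in a "pre-post-follow-up repeated measures intergroup design with a 1:1:1 allocation ratio" (Study Design and Settings). On delivery of face-to-face ACT, the intervention section states: "This intervention will be carried out in groups of approximately 10 people". Patients in the ACT + app arm "will receive the same intervention program as the face-to-face group described before, with the same characteristics", so that arm is treated in groups too. The waitlist is different: "This group will receive the usual care during the essay". It is offered grouped ACT + app only after the post-treatment assessment (T1).

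The Sample Size section takes as inputs an f of 0.25, power 0.80, alpha 0.05, a correlation of 0.5 between repeated measures and 10% dropout. It concludes that "a total sample of 102 participants is required", or 34 per arm, raised to 38 per group for dropout. It mentions no ICC, cluster size or design effect.

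The Statistical Methods section says "we will use mixed linear models, since these models are more precise than the repeated measures ANOVA". It describes change over time and differences between arms, with missing data handled by maximum likelihood. It names no effect for therapy group or therapist. The limitations in the Discussion do not mention clustering.

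**The concern.** Members of one therapy group sit through the same eight weekly sessions, discussions and exercises together. Their outcomes may therefore be more alike than those of patients in different groups. The design is partially nested: both ACT arms are clustered, and the waitlist is not clustered up to T1.

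Two separate consequences follow if the ICC is above zero:

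- **Sample size.** A calculation that assumes independence overstates power. It does not itself affect type I error.
- **Analysis model.** A model that leaves out therapy group understates the standard errors of comparisons involving the ACT arms, which inflates type I error.

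The first hypothesis is the most exposed, because ACT + app versus ACT compares roughly four therapy groups with four others. A chance difference between a few groups could pass for an effect of the app.

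**Working it through.** **1. Reproduce the stated sample size.** Inputs from the Sample Size and Study Design sections: 3 arms, 4 assessments, f = 0.25, within-patient correlation 0.5, alpha 0.05. The between-arms F test in repeated-measures ANOVA has noncentrality

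λ = f² × N × 4 / (1 + 3 × 0.5) = 0.0625 × N × 4 / 2.5 = 0.1 × N, with 2 and N − 3 degrees of freedom.

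At N = 102, λ = 10.2 and power is 0.811. At N = 99 it is 0.798. So 102 is the smallest N with equal arms that reaches 0.80, and it contains no allowance for therapy groups. The 0.5 is a correlation between visits of one patient and cannot stand in for correlation between patients.

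**2. Number and size of therapy groups.** At about 10 per group, 38 enrolled per arm make about four groups. With 34 evaluable, the average is 34 / 4 = 8.5 per group.

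**3. Formulas.** The ICC is an assumption.

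- Design effect in an ACT arm: DE = 1 + (8.5 − 1) × ICC
- Effective size of an ACT arm: 34 / DE
- Type I error when therapy group is ignored: 2 × [1 − Φ(1.96 / √V)]. V = DE for ACT + app versus ACT. V = (DE + 1) / 2 for an ACT arm versus waitlist, where only one side is clustered.

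| Assumed ICC | DE | Effective n of 34 | Type I error, ACT + app vs ACT | Type I error, ACT vs waitlist (T1 only) |
|---|---|---|---|---|
| 0.01 | 1.08 | 32 | 5.9% | 5.4% |
| 0.02 | 1.15 | 30 | 6.8% | 5.9% |
| 0.05 | 1.38 | 25 | 9.5% | 7.2% |
| 0.10 | 1.75 | 19 | 13.8% | 9.5% |

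Worked example at ICC 0.05: DE = 1 + 7.5 × 0.05 = 1.375. For ACT + app versus ACT, 1.96 / √1.375 = 1.671, which gives 9.5%. For ACT versus waitlist, V = 2.375 / 2 = 1.1875 and 1.96 / √1.1875 = 1.799, which gives 7.2%.

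**4. Check by simulation.** 40,000 replicates per ICC, 34 per arm, therapy groups of 9, 9, 8 and 8, single-visit t test ignoring therapy group. At ICC 0.01, 0.05 and 0.10 the rejection rate under the null was 5.8%, 9.5% and 14.3% for ACT + app versus ACT, and 5.4%, 7.0% and 9.7% for ACT versus waitlist. These agree with the formula.

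**5. Rough effect on the planned power.** The effective total is 34 + 2 × (34 / DE) = 97.3, 93.1, 83.5 and 72.9. Putting λ = 0.1 × effective total into the F test of step 1, with 2 and 99 degrees of freedom, gives power of about 0.79, 0.77, 0.72 and 0.66, against 0.81 without clustering. This is only indicative: it applies one design effect at every visit, although T0 precedes the therapy groups, and it makes no charge for estimating a between-group variance from few groups.

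**The case against.** The strongest objection is that the article does not fix the random-effects structure at all. It specifies mixed linear models, the usual home for a therapy-group effect, and gives no random effects or covariance structure. A fuller plan that is not shown could include the term. This stands as far as it goes: one may say that the article names no such term, but not that the analysis will certainly omit it. It does not rescue the sample size, which the article does fix and which reproduces with independent patients.

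Three stronger readings are tempting and are not supported:

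- **That type I error is inflated, without qualification.** Inflation requires a positive ICC and a model without the term. The documents give no ICC, and at 0.01 the inflation is under one percentage point. Nor does the unadjusted sample size cause it; that costs power.
- **That patients in a group also share a therapist effect.** The Interventions section does not give the number of therapists or their assignment to groups. If one therapist led every group, therapist would add no between-group variance. The common manual, training and supervision also aim at uniform delivery. The case rests on shared sessions and group process alone.
- **That the waitlist figures apply throughout follow-up.** They hold at T1 only. Afterwards waitlist patients may join therapy groups themselves.

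A further fair objection is that about four groups per arm give little information on a between-group variance. That limits the remedy but is no reason to leave the term out.

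**Conclusion.** The point holds in a conditional form. It is firm that the 102 assumes independent patients although two of the three arms are treated in groups, so the stated 0.80 is reached only if the ICC is zero. It is also the case that the model, as described, names only time and arm. Fitted that way, it would give standard errors that are too small for any positive ICC. The size depends on an ICC that has to be assumed: slight at 0.01, close to a doubling of the nominal error for ACT + app versus ACT at 0.05, and larger at 0.10. Comparisons with the waitlist at T1 are affected less. The figures assume four equal groups of 8.5 evaluable patients per ACT arm, equal total variance in all arms and a normal approximation. This should be corrected, chiefly for the first hypothesis.

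**What to change.** - **Data.** Record the therapy group of every patient prospectively, including the group that a waitlist patient joins after T1. If this is not captured during delivery, it may not be recoverable.
- **Model.** Add a random effect for therapy group in the two ACT arms (partially nested model). Up to T1 each waitlist patient is their own cluster; for T2 and T3, those who cross over belong to the group they joined. Use Satterthwaite or Kenward-Roger degrees of freedom.
- **Sample size.** Restate the power for the planned N over a declared ICC range, for example 0.01 to 0.10, in place of an unconditional 0.80.

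The cost is one extra variable, one model term and a short power table. Confidence intervals will be wider. With about four groups per arm the variance component will be imprecise and may be estimated at zero, so the nominal error rate may be only partly restored. The report should state this as a limitation.
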